### Study population and eligibility criteria

All children suffering from SAM, without any complications, and aged 6–59 months, are eligible for inclusion in the present trial. Participants will be screened using weight-for-height/length *z*-score and mid-upper arm circumference (MUAC) as screening criteria. The criteria of the World Health Organization (WHO) will be used to diagnose edema among children. WHO defines children with grade 1–2 bilateral edema and a weight-for-height/length *z*-score of < − 3 standard deviations (SD) or MUAC of < 11.5 cm who are otherwise clinically healthy, aware, and with a decent appetite as children with SAM [28]. Trained healthcare staff including nurse, childcare worker, and doctor will assess the children for eligibility. MUAC will be assessed using WHO’s MUAC colored tapes in centimeters (cm), while weight-for-height/length *z*-score and weight of children will be assessed in grams (g) with minimal and light clothing using UNISCALE, and height will be measured using a standard measuring tape in cm(s) and then will be compared with the grading of *z*-score chart. All the anthropometric measures will be taken thrice to reduce information bias. Additionally, all the instruments that will be used for taking measurements will be checked for accuracy and zero precision beforehand. All eligible participants will be recruited following a pre-defined inclusion and exclusion criteria (Table 1).

**Table 1 Tab1:** Inclusion and exclusion criteria

*Inclusion criteria*	*Exclusion criteria*
Ages 6–59 months at enrolment	
Acute malnutrition without complications, as defined by the WHO (i.e., children with MUAC < 115 mm or weight-for-height *z*-score < − 3 or grade 1–2 bilateral edema who will be clinically well and alert with good appetite	Presence of any complications of severe malnutrition (severe dehydration, severe anemia, severe pitting edema, anorexia, hypothermia, high pyrexia, acute lower respiratory infection, or hypoglycemia) or immune compromised
Parental consent for the child to participate	Declined parental consent
Healthy children without any chronic or acute illness	Children on antibiotic treatment for any disease in the last 3 months

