### Outcome parameters

All the assessments will be carried out by a trained staff unrelated to the enrolment and allocation procedures. The primary outcome of the trial is to examine the microbiome diversity of malnourished children, to compare it with healthy children, and to evaluate the effect of RUTF plus prebiotics on the microbiome diversity of malnourished children (Table 3). For achieving the primary outcome, 5 g stool sample of the children will be collected for DNA extraction using QIAamp DNA Stool kit (Qiagen, Hilden, Germany) for examining the microbiome diversity through 16 Svedberg (S) ribosomal ribonucleic acid gene sequencing.

**Table 3 Tab3:** Primary outcome parameter

*Outcome measure*	*Measure description*	*Time frame*
Microbiome diversity	Microbiome diversity examination among malnourished children using 16 Svedberg (S) ribosomal ribonucleic acid gene sequencing. The microbiome diversity index measures the diversity of microbial species in malnourished children’s gut microbiota, comparing it to reference and control populations. Higher values indicate greater diversity, providing insights into malnutrition’s impact on gut microbiota composition	8 weeks

For the accomplishment of secondary outcome parameters, anthropometric measures of the children, including their height, weight (for calculating weight-for-height/length z-score), and MUAC will be assessed by a trained healthcare staff. For assessing neurodevelopment of children, the Malawi Development Assessment Tool (MDAT) will be used that is considered to be one of the most valid tools for assessing child development for ages 0–59 months measuring their motor, language, social, and cognitive development [29], while for assessing the muscle mass accumulation, Body Stat Analyzer will be used (Table 4).

**Table 4 Tab4:** Secondary outcome parameters

*Outcome measures*	*Measure description*	*Time frame*
Anthropometric measurements	Change in the mean weight-for-height/length *z*-score and MUAC in children with complicated severe acute malnutrition who have been taking prebiotics supplementation for 8 weeks	8 weeks
Neurodevelopment assessment	Impact assessment of prebiotic supplementation on children’s neurodevelopment using the Malawi Development Assessment Tool	8 weeks
Muscle mass accumulation	The study investigates the impact of prebiotic consumption on body composition changes using the Body Stat Analyzer as a quantitative measurement tool	8 weeks

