Starch to placebo comparator group		x	x	x	x	x	x	x	x	
RUTF plus starch to active comparator group		x	x	x	x	x	x	x	x	
RUTF plus prebiotics to experimental group		x	x	x	x	x	x	x	x	
*Assessments*										
Sociodemographic characteristics	x									
Anthropometric measures (weight, height, MUAC)	x								x	
Fecal samples	x								x	
Malawi Developmental Assessment Tool	x								x	
Body stat analyzer	x								x	
Outcome analysis										x

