## Conclusions

Conclusively, the results of the present trial are expected to indicate RUTF plus prebiotic as a cost-effective therapy for improving the gut microbiome diversity of SAM children and as a more effective therapy for treating SAM children as compared to RUTF individually. GOS present in prebiotics is proven to have positive effects on growth of bifidobacterial, stool consistency, bowel function and transit time, support of natural defenses, and mineral absorption that could also provide beneficial results for treating the malnutrition among children. This is the first trial that evaluates the effect of prebiotics on the gut microbiome diversity of SAM children, as per our knowledge. Despite of its limitations, the results of the present trial would provide useful insights and high-quality data for the treatment and management of SAM children by evaluating the effect of RUTF plus prebiotic on the gut microbiome diversity of children, leading to medical evidence for designing large-scale studies.

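### The oedema entry criterion is stated in two conflicting ways and oedema is not rechecked at week 8, so weight-for-height change mixes fluid loss with tissue gain

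*Protocol article*

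**What the plan says.** **Entry.** In the protocol article, Study population and eligibility criteria, Table 1 admits a child with a low MUAC, or a WHZ below −3, "or grade 1–2 bilateral edema who will be clinically well and alert with good appetite". Severe pitting oedema is an exclusion; grades 1–2 are admitted. The paragraph above the table reads differently: "WHO defines children with grade 1–2 bilateral edema and a weight-for-height/length" z-score below −3, or a MUAC below 11.5 cm. That paragraph names WHZ and MUAC as the screening criteria, and also states: "The criteria of the World Health Organization (WHO) will be used to diagnose edema among children".

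**Follow-up.** Table 5 (Data collection) spells out what is measured at weeks 0 and 8: "Anthropometric measures (weight, height, MUAC"). Oedema is not in that row or any other.

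**Outcomes.** "The primary outcome of the trial is to examine the microbiome diversity of malnourished children". The anthropometric secondary outcome in Table 4 is "Change in the mean weight-for-height/length" z-score and in MUAC over 8 weeks. Neurodevelopment and body composition complete the table. No outcome classifies a child as recovered.

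**Analysis.** Statistical analysis compares the three groups by ANOVA or Kruskal–Wallis, and tests change within a group by paired t-test or Wilcoxon. The planned regression concerns sociodemographic characteristics.

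**Expected conclusion.** The Conclusions expect RUTF plus prebiotic to prove cost-effective and to emerge "as a more effective therapy for treating SAM children as compared to RUTF individually".

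**The concern.** Oedema is fluid weight. As it clears, weight falls while tissue gain pushes weight up, so in a child who entered with oedema a given WHZ change does not mean what it means in a wasted child. Averaging the two kinds of child gives a figure that understates tissue gain by an unknown amount.

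Three readings are exposed: the paired change within each RUTF arm; the contrast of those arms with healthy children, who have no oedema to lose; and, less seriously, the randomised contrast of RUTF plus GOS with RUTF plus starch. If fluid affects the body analyser, the body-composition outcome has the same problem; the article does not describe how the device measures, so this remains a possibility.

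The week-8 sign matters most. A later analysis plan can add a covariate, but it cannot recover an observation that was not made. The two entry definitions add to the difficulty, because the share of children with oedema depends on which one sites apply.

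**Working it through.** **1. Entry definitions side by side.** Table 1: MUAC < 115 mm, *or* WHZ < −3, *or* grade 1–2 oedema. Prose: grade 1–2 oedema *and* WHZ < −3, *or* MUAC < 11.5 cm. A child with grade 1 oedema, WHZ −2 and MUAC 12 cm enters under Table 1 and not under the prose. Children with oedema can enter under either, so the fluid problem exists in both cases; only their share changes.

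**2. The plan's own figure, used here for the arm size.** For a balanced one-way ANOVA with k = 3, f = 0.25 and alpha 5%, noncentral F power is 79.7% at n = 52 and 80.5% at n = 53. The stated 53 per group reproduces. The plan gives no figure for oedema.

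**3. Assumed inputs (none in the documents).** Child of 7 kg with 0.3–0.5 kg of oedema fluid; weight SD at that length 0.65 kg; oedema share p = 10–20%; SD of WHZ change 1.0 without oedema.

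**4. Fall per child with oedema.** s = fluid / weight SD: 0.3/0.65 = 0.46 z; 0.5/0.65 = 0.77 z.

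**5. Shift in each RUTF arm mean if all oedema clears.** p × s: 0.10 × 0.46 = 0.05 z; 0.20 × 0.77 = 0.15 z. This goes in full into the paired within-arm change and the contrast with the healthy group.

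**6. Randomised contrast.** Bias = −p × s × (share cleared by week 8 under GOS − share cleared under starch).
- Equal clearance: the bracket is 0, so the expected bias is 0.
- Illustration with p = 20% and a 50-point difference in clearance: 0.20 × 0.50 = 10 points of all children, and 0.10 × (0.46 to 0.77) = 0.05–0.08 z against the arm that clears more.

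**7. Chance imbalance at entry, 53 per arm.** The SD of the difference in oedema share is √(2p(1−p)/53): 5.8 points at p = 10%, 7.8 points at p = 20%. A 10-point imbalance moves the contrast by 0.05–0.08 z. The standard error of the contrast is √(2/53) = 0.19, so this is under half a standard error.

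**8. Precision.** Variance becomes 1 + p(1−p)s². A difference of 0.544 z has 80% power at SD 1.0. Power = Φ(0.544/(SD × 0.194) − 1.96).

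| p | s | shift in each arm mean | SD | power |
|---|---|---|---|---|
| 5% | 0.5 | −0.025 | 1.006 | 79.5% |
| 10% | 0.46 | −0.05 | 1.009 | 79% |
| 20% | 0.77 | −0.15 | 1.046 | 76% |
| 10% | 1.0 | −0.10 | 1.044 | 76.5% |
| 20% | 1.0 | −0.20 | 1.077 | 74% |
| 50% | 1.5 | −0.75 | 1.250 | 61% |

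The first and last rows are outer bounds. The result is dilution of the randomised contrast.

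**9. Conclusions against the tables.** Tables 3–5 contain no cost measure. Table 2 has no arm that receives RUTF alone; the comparator receives RUTF plus starch.

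**The case against.** The best defence is randomisation. Malnourished children are allocated at random between the two RUTF arms, so a loss of fluid common to both cancels in expectation. A chance imbalance is ordinary sampling variation, already covered by the standard error. The primary outcome is microbiome diversity, and neither it, MUAC nor the neurodevelopment tool depends on weight. All of this stands, and it rules out the inference that the treatment comparison cannot be tested.

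A reader might also infer that a child who sheds oedema is counted as a treatment failure. The documents do not support that: no recovery or responder endpoint exists, only mean changes. Nor does faster clearance by itself make the prebiotic look worse. Measurements are taken only at weeks 0 and 8, so what matters is a difference in oedema still present at week 8, and nothing in the article suggests one.

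It can be said too that covariates and subgroups belong in an analysis plan, and that an article condenses the full protocol, which is available on request. This holds for the choice of model. It holds less well for the schedule, because Table 5 itemises the week-8 anthropometry and omits the one entry sign that is not a measurement of size. If the full protocol already records it, the article needs only aligning.

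Finally, the Conclusions state an expectation and do not define an analysis. That is fair, and the wording there is a side point.

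**Conclusion.** The point holds as a moderate one about secondary outcomes. Two things are certain from the text: the entry definitions conflict, and oedema is assessed at screening but not scheduled or analysed at week 8. From these it follows, on the premise that clearing oedema lowers weight, that pooled WHZ change understates tissue gain within each RUTF arm and against the healthy group. In the randomised contrast the cost is precision, with bias only if residual oedema differs between arms.

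The size is unknown. The figures of 0.05–0.15 z per arm mean and 76–79% power in place of 80% rest on the assumed share, fluid mass and SDs. It should not be stated as fact that children enter on oedema alone, since only one of the two definitions says so. The absence of a recovery endpoint is a design choice in a microbiome trial and is not an error here.

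**What to change.** 1. Reconcile the prose and Table 1 so that one entry definition applies at both hospitals. Which one is for the investigators to decide.
2. Record oedema grade at weeks 0 and 8 and add it to the anthropometry row of Table 5.
3. In the WHZ and body-composition comparison of the two RUTF arms, include entry oedema as a factor. Add a sensitivity analysis in children without oedema at entry, and report how many in each arm still have oedema at week 8.
4. In the Conclusions, limit the expected finding to the outcomes measured, remove the cost-effectiveness claim, and name RUTF plus starch as the comparator.

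The cost is one brief check at a visit where the child is already measured, one model term and some text edits. The oedema subgroup will be small and should be reported descriptively. No change to treatment is involved.

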### Sample size estimation

For sample size estimation, a balanced one-way analysis of variance power calculation with R software was used, and a minimum of sample of 53 participants was calculated for each group using 5% significance level, 80% power of study, 0.25 effect size (*f*) and 3 as *k* value (Fig. 2).

**Fig. 2 Fig2:**
[figure not shown]
Sample calculation using R software

A calculated sample of 159 participants (53 participants each arm) is further inflated by 10% to account for attrition due to loss to follow-up, making a total sample of 174 participants with 58 participants required to be recruited in each arm. For achieving adequate participant enrolment to reach target sample size, community mobilization in the nearby areas of the selected hospitals through lady health workers will be carried out with the support of IRMNCH & Nutrition Program.

### Informed consent

Informed consent will be taken from the parents/guardians of the children on a written consent form. The purpose of the trial and the potential adverse reactions (i.e., allergies) of the treatment modalities will be clearly communicated to them. Upon their approval, thumb impression will be taken on the written consent form. The process of taking consent from each parent/guardian will be conducted in the presence of at least one witness.

### Randomization and allocation

Children suffering from acute malnutrition, otherwise healthy, aged 6–59 months, and fulfilling the inclusion criteria will be recruited randomly to one of the two arms of the present trial for 8 weeks, i.e., experimental and active comparator groups. However, healthy children with matched sex and age will be recruited from the vaccination centers of the research sites to the placebo comparator group as healthy controls. The participants in all groups will be recruited in equal allocation ratio (1:1:1) with no restriction of block size. A statistician unaware of the study method will generate the random numbers and allocate the participants to study groups by assigning unique code to them (i.e., SAM children to experimental and active comparator group and healthy children to placebo comparator group). All the participants will be given a recruitment card with their unique identity code mentioned on it.

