**Methods:**

The study is designed as a prospective, double-blinded, triple-armed, multi-centered randomized controlled trial, with 6–59 months old uncomplicated SAM children recruited to the experimental group receiving ready-to-use therapeutic food (RUTF) plus prebiotics and the active comparator group receiving RUTF plus starch for 2 months duration (8 weeks). Healthy children with matching age and gender will be recruited to placebo comparator group and will receive starch as a placebo during the study period. A total of 58 participants will be recruited to each arm with 1:1:1 allocation ratio following a pre-defined inclusion and exclusion criteria. The results of the gut microbiome diversity will serve as the primary outcome, while weight-for-height/length *z*-score, mid-upper-arm circumference, neurodevelopment assessment, and body mass accumulation will serve as the secondary outcome. Data collection and evaluations will be conducted at baseline and at the end of the trial (week 8), while the safety monitoring will be conducted at every second week. For analysis, the principles of intention-to-treat will be followed.

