Furthermore, Statistical Package for Social Science (SPSS) version 24 will be used for evaluating the change in weight-to-height/length *z*-score, MUAC, neurodevelopment assessment, and muscle mass accumulation among trial participants. Firstly, for descriptive analysis, percentages and frequencies will be presented of qualitative variables (gender of the child, ethnicity, breast feeding history, and mother’s dietary habits), while mean ± SD (in case of normally distributed variables) and median ± inter-quartile range (IQR) (in case of skewed variables) will be given for quantitative variables. Furthermore, the association of the sociodemographic characteristics of the children and mothers with the weight-to-height/length z-score, MUAC, neurodevelopment assessment, and muscle mass accumulation among children will be explored through regression analysis. For comparing the outcomes between three trial groups, test of analysis of variance (ANOVA) will be used with Scheffe and Games-Howell test for post hoc multiple comparisons in case of normally distributed data; otherwise, Kruskal–Wallis test will be applied, while for analyzing the data of repeated measures within the same groups, paired-sample *t*-test (for normally distributed datasets) or will Wilcoxon test (for non-normally distributed datasets) will be applied. All the tests will be applied at 95% confidence interval (CI) by an independent statistician blinded to the study.

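### Healthy controls are matched on age and sex, but the only three-group test named uses neither factor, so SAM-versus-healthy intervals would tend to be too wide

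*Protocol article*

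**What the plan says.** Four places in the Protocol article bear on this.

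- **Design.** The third arm is not randomised. Under Randomization and allocation, "healthy children with matched sex and age will be recruited from the vaccination centers of the research sites". The abstract says the same: "Healthy children with matching age and gender will be recruited to placebo comparator group". The age range in Table 1 is wide: "Ages 6–59 months at enrolment". The article does not say whether matching is individual or by frequency, or to which SAM arm.
- **Estimand.** Under Outcome parameters: "The primary outcome of the trial is to examine the microbiome diversity of malnourished children, to compare it with healthy children". The contrast with the matched arm is therefore part of the primary outcome.
- **Test.** Under Statistical analysis: "For comparing the outcomes between three trial groups, test of analysis of variance (ANOVA) will be used with Scheffe and Games-Howell test", with Kruskal–Wallis as the non-normal alternative. Neither carries age, sex or matched set. The sample size rests on the same model, a balanced one-way ANOVA.
- **Where age and sex do appear.** They are recorded at baseline (Data collection). Sociodemographic factors enter a regression, but it is exploratory, separate from the group comparison, and limited to the four secondary outcomes.

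**The concern.** Matching makes the healthy and SAM groups alike on age and sex. Whatever part of the outcome those factors explain then cancels from the difference in means. A one-way ANOVA does not know this. It leaves that part in the residual and computes the standard error as if the groups were independent samples. The reported interval is then wider than the design warrants and the p-value larger.

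There is a second side. This contrast has no randomisation behind it. If the matching is loose, any remaining difference in age or sex between healthy and SAM children passes straight into the estimate, and the named test cannot remove it.

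**Working it through.** **Inputs from the article.** α = 0.05, power 0.80, f = 0.25, k = 3, n = 53 per group, 58 per arm recruited. **Assumed:** R², the share of outcome variance explained by age and sex. The article gives no value, so a range of 0 to 0.50 is shown.

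**1. The plan's own figure.** The noncentrality is k·n·f² = 3 × 53 × 0.0625 = 9.94, with 2 and 156 degrees of freedom. Power is 0.805 at n = 53 and 0.797 at n = 52, so 53 per group reproduces.

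**2. The contrast.** Take the healthy mean minus the average of the two SAM means. In outcome SD units, the ANOVA standard error is √(1/53 + 1/106) = √(1.5/53) = 0.168.

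**3. Effect of matching.** With good matching the true standard error is 0.168 × √(1 − R²), so the ANOVA overstates it by a factor of 1/√(1 − R²):
- R² = 0.10: 1/√0.90 = 1.05
- R² = 0.30: 1/√0.70 = 1.20
- R² = 0.50: 1/√0.50 = 1.41

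**4. Simulation.** There were 20,000 trials per scenario with 53 per arm, a normal outcome and one continuous matching factor. The contrast was tested two-sided at 5%, unadjusted or by ANCOVA. For power, f = 0.25 was placed entirely in the healthy arm. With one of three equal groups shifted by d, f = d√2/3, so d = 3 × 0.25/√2 = 0.53 SD. Results for individually matched triplets:

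| R² | SE ratio | Type I error, unadjusted | Type I error, adjusted | Power, unadjusted | Power, adjusted |
|---|---|---|---|---|---|
| 0 | 1.00 | 0.048 | 0.048 | 0.882 | 0.882 |
| 0.10 | 1.06 | 0.038 | 0.048 | 0.896 | 0.913 |
| 0.30 | 1.20 | 0.020 | 0.050 | 0.919 | 0.964 |
| 0.50 | 1.41 | 0.006 | 0.049 | 0.952 | 0.994 |

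Frequency matching to the pooled SAM children gives nearly the same SE ratios (1.05, 1.21 and 1.42 at R² = 0.10, 0.30 and 0.50).

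**5. Control run without matching.** When all three groups are drawn independently from one age distribution, the ratio at R² = 0.30 is 0.999 and the unadjusted type I error is 0.050. The mismatch therefore comes from the matching. For the same reason, an unadjusted test between the two randomised arms is valid.

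**6. Imperfect matching.** If the matching factor differs by δ of its own SDs between healthy and SAM children, the unadjusted estimate is shifted by √R² × δ outcome SDs. The article gives no matching tolerance, so no value of δ can be put in.

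The figures apply to a single contrast under ANOVA. The Scheffé correction and Kruskal–Wallis were not simulated.

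**The case against.** - **The ANOVA may not be the primary analysis.** Its sentence sits in the SPSS paragraph, which opens with the four secondary outcomes. The microbiome text lists diversity indices and names no between-group test. This stands as a caution: a reader might infer that ANOVA is explicitly assigned to diversity, and it is not. The link rests on the ANOVA-based sample size, the general wording about comparing outcomes across three groups, and the absence of any other test. If the ANOVA covers only secondary outcomes, the same matched arm is still in it.
- **Covariates are usually left to the analysis plan.** This is true in general. Here, though, the article states both the matched design and the test, and the two do not fit. The point rests on what is stated.
- **The error is harmless.** In part this stands. A reader might infer invalid inference or false positives. With sound matching the opposite holds: type I error falls below 5%, and at R² = 0 nothing is wrong.
- **The loss might be read as throwing away up to half the sample.** It is not. Matching still shrinks the true variance, and only the estimated standard error is too large. At R² = 0.50 the unadjusted power is 0.95. Truly halving the sample in that case would give about 0.88 (0.53/0.168 ≈ 3.15 standard errors).
- **A mismatch might be thought unavoidable with 58 healthy against 2 × 58 = 116 SAM children.** The article does not support this. It leaves 1:2 and frequency matching open and gives no evidence that matching will be poor.

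**Conclusion.** The point holds as a mismatch between design and test, limited to the SAM-versus-healthy contrast. Provided that matching is achieved and age and sex predict the outcome, the named test gives a standard error about 5%, 20% or 41% too large at R² of 0.10, 0.30 or 0.50. The corresponding type I error is about 0.038, 0.020 or 0.006. The power cost is modest: 0.92 against 0.96 at R² = 0.30 for a 0.53 SD difference. These sizes depend on an R² that the article does not supply, and nothing in it supports the upper end in particular.

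The conservative direction is conditional on good matching. With loose matching the concern becomes uncorrected confounding by age or sex, of unknown size and sign.

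The randomised comparison of RUTF plus prebiotics with RUTF plus starch is not invalidated, and the planned sample size can stay.

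**What to change.** State whether matching is individual or by frequency, and to which SAM children. Then specify that the SAM-versus-healthy comparison, for diversity and for the secondary outcomes, is made by linear regression (ANCOVA) with age in months and sex as covariates. If matching is individual, a matched-set term can be used instead. Say explicitly which test applies to the diversity indices.

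Both covariates are already recorded at baseline. The cost is a change of wording and slightly more analysis work, with no new data and no change in sample size. It should be settled before outcome data are seen.

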### Study setting

The trial will be conducted at two public sector District Health Quarter (DHQ) level hospitals in Lahore, i.e., Government Mian Mir DHQ and Government Samnabad DHQ. Permissions will be taken from the relevant authorities of the hospitals. These two hospitals are selected as currently Integrated Reproductive Maternal Newborn, Child Health (IRMNCH) & Nutrition Programs are running in these hospitals with a high patient load.

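### The stated allocation does not guarantee 58 children per SAM arm, and hospital enters neither the allocation nor the group comparison as described

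*Protocol article*

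**What the plan says.** The sample size section asks for a one-way ANOVA "using 5% significance level, 80% power of study, 0.25 effect size (*f*) and 3 as *k* value", finds 53 per group, and then inflates for loss to follow-up, "making a total sample of 174 participants with 58 participants required to be recruited in each arm".

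The Randomization and allocation section states that participants "will be recruited in equal allocation ratio (1:1:1) with no restriction of block size". The random numbers come from a statistician. The same section makes clear that only SAM children are randomised: they "will be recruited randomly to one of the two arms of the present trial for 8 weeks, i.e., experimental and active comparator groups". The healthy children are an age- and sex-matched group recruited from vaccination centres. So the allocation question concerns 116 SAM children (2 × 58) at 1:1.

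Under Study setting: "The trial will be conducted at two public sector District Health Quarter (DHQ) level hospitals in Lahore". No stratification factor is named. The Statistical analysis section compares the three groups by ANOVA with post hoc tests, or by Kruskal–Wallis. It also plans regressions on sociodemographic characteristics. Hospital appears in none of these.

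**The concern.** The article sets a target for each arm and then describes an allocation that need not reach it. On the most direct reading, the phrase about block size means that there are no blocks, so arm totals are left to chance. The wording also fits blocks whose size is not fixed, or a list balanced in advance. The text does not settle which is meant.

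Hospital is a separate matter. With two sites and a stool microbiome outcome, hospital could plausibly be related to diet, water and background exposure, although the article gives no data on this. Nothing described keeps the hospital mix similar between the prebiotic and starch arms, and nothing in the described analysis removes the effect of a difference. At stake are some avoidable noise in the one randomised comparison and a published sentence that cannot be followed unambiguously.

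**Working it through.** **The plan's own figure.** Balanced one-way ANOVA, k = 3, f = 0.25, alpha = 0.05, noncentral F with noncentrality f² × 3n. Power is 0.797 at n = 52 and 0.805 at n = 53, so 53 per group reproduces. Inflation: 53 × 1.1 = 58.3 and 159 × 1.1 = 174.9, in line with 58 and 174.

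**Arm sizes under simple randomisation.** X, the number in one SAM arm, is Binomial(116, 0.5), with SD √116 / 2 = 5.4.

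| Quantity | Result |
|---|---|
| P(X = 58) | 7.4% |
| Central 95% range of X | 47 to 69 |
| P(smaller arm below 53) = 2 × P(X ≤ 52) | 30.7% |
| P(smaller arm below 48) = 2 × P(X ≤ 47) | 5.1% |

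**Power cost of unequal arms.** Two-sample t test of the SAM arms, two-sided 5%, noncentrality d / √(1/n₁ + 1/n₂). The article gives no standardised difference for this pair; d = 0.5 is assumed.

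| Split | Noncentrality | Power |
|---|---|---|
| 58:58 | 2.69 | 76.1% |
| 53:63 | 2.68 | 75.8% |
| 47:69 | 2.64 | 74.6% |

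The loss is 0.3 points at 53:63 and 1.5 points at the edge of the 95% range.

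**Hospital mix.** The split of SAM children between hospitals is not given, so three splits are assumed. The measure is the absolute difference between the SAM arms in the share of children from one hospital (400,000 simulated allocations each).

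| Assumed split | Simple: P(gap ≥ 10 points) | Simple: 95th percentile | List fixed at 58:58, no strata: P(gap ≥ 10 points) |
|---|---|---|---|
| 58/58 | 31% | 19 points | 35% |
| 77/39 | 24% | 17 points | 24% |
| 87/29 | 22% | 16 points | 20% |

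Fixing the arm totals does not help the hospital mix; only strata do.

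**What a gap does to the estimate.** If the two hospitals differ in mean outcome by δ, an unadjusted arm difference shifts by gap × δ: 0.10δ at 10 points and 0.19δ at 19 points. The article gives nothing from which δ could be estimated.

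**After stratified blocks.** With an assumed largest block of 6, imbalance is at most 3 children per hospital and 6 overall, so the worst case is 55:61. With equal hospitals, a 3-child imbalance shifts the hospital share by about 3/58, or 5 points.

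**The case against.** Four points can be made for the plan.

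1. The phrase is ambiguous. It mentions block size next to an equal ratio, which is an odd way to declare simple randomisation. Under blocks of varying size, or a list fixed at 58:58, the arm-size figures largely fall away. This stands, so those figures are conditional on one reading.

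2. A reader might infer that the design cannot deliver 58 per arm, or that it would have to close a full arm and make the last allocations predictable. The article supports neither. Simple randomisation gives 1:1 in expectation and 58:58 in 7.4% of lists. Nothing says that an arm would be closed, or that the trial fails at, say, 56:60.

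3. A reader might infer that hospital confounds the comparison. It does not: chance imbalance under concealed randomisation leaves the comparison unbiased. Both sites are public hospitals in one city with the same nutrition programme, and no hospital effect is documented. This stands; the cost is precision only.

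4. A condensed article may leave strata and model terms to the full protocol. This stands in part. The article does not merely stay silent, though: it describes the restriction on allocation, and that description secures neither arm totals nor hospital balance.

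One further figure needs care. With 10% independent loss, both SAM arms keep at least 53 children in only 7.4% of realisations under simple randomisation. A perfect 58:58 split gives only 22%, because 58 × 0.9 = 52.2 is already below 53, and 55:61 gives 6.6%. Much of that shortfall comes from thin inflation and chance attrition, so it should not be charged to the allocation method.

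**Conclusion.** The point holds as a cheap improvement. The allocation sentence needs to be reconciled with the target of 58 per arm: if it means simple randomisation, it does not guarantee that target, although a power loss of about 1.5 points at the edge of the 95% range is no threat to the trial. The hospital point does not depend on how the sentence is read, provided no strata exist elsewhere. A gap of at least 10 points between the SAM arms then has a probability of about 20 to 35%, and the described analysis does not adjust for it.

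The conclusion rests on 116 randomised SAM children, the assumed hospital splits, d = 0.5 for the power figures, and the article being a fair account of the full protocol. The practical loss could be nil if the hospitals do not differ on the outcome.

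**What to change.** Replace the block-size phrase with an explicit method: permuted blocks of random size, stratified by hospital, 1:1 for prebiotic versus starch, SAM children only, prepared by the same statistician. Describe the healthy group separately as matched and not randomised, so that the 1:1:1 ratio is not read as a three-way randomisation. Include hospital as a factor in the prebiotic versus starch comparison; if a rank test is used, stratify it by hospital.

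The article expected recruitment to run from June to July 2024. If allocation is complete, report the method actually used and the hospital counts by arm, and add the hospital adjustment before unblinding.

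The cost is one extra list, one model degree of freedom and slight predictability near the end of a block, which random block sizes and coded packets keep small.
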